### Prospective memory task

To examine the neural substrates of event-based and time-based prospective memory, we will use a computerized task in the MR scanner [32], which will be presented with PsychoPy (v2021.1.2). The task will consist of four blocks: During the first and the third block, participants will perform a 1-back working memory task (as an ongoing-task), during which they will need to decide whether the current image is the same as the image presented just before (Fig. 2). Pseudorandom sequences of 238 Snodgrass & Vanderwart [33] pictures will be displayed on a screen for 2–3 s, followed by a 1–2 s inter-stimulus interval, used as a temporal jitter. During the second and the fourth block, a prospective memory task will be added to the ongoing task. One block will contain the event-based task and the other block the time-based task. The order will be counterbalanced across participants. In the event-based task, participants are asked to press a button whenever an animal appears on the screen (Fig. 2). Every answer that occurs within 5 s following the presentation of an animal will be considered as a prospective memory hit [32, 34]. In the time-based task, participants are asked to press a button whenever one minute has passed (Fig. 2). To monitor the time, they will be able to press another key to display a clock for 3 s in the upper left corner of the screen. Every correct response occurring ± 2.5 s around each target time will be counted as a prospective memory hit [32, 34]. Each prospective memory block will consist of 158 trials; out of these, 54 trials will be ongoing 1-back hits (i.e., trials in which the picture will be identical to the previous one), and 10 prospective memory cues (i.e., one every minute at 1:00, 2:00, 3:00… until 10:00) so that both tasks are similar. Each prospective memory block will last 10.5 min.

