**Fig. 2 Fig2:**
[figure not shown]
Procedure of the prospective memory paradigms. Each prospective memory task (i.e., event-based, or time-based) consists of an ongoing task (a 1-back task) either alone or in combination with a prospective memory task, where participants additionally need to respond to certain events (here: animals) or after a certain amount of time has passed (here: every minute). In the incentive group, participants will start with an initial amount of money (i.e., 5 Swiss Francs per task) and they will lose 0.50 Swiss Francs for every missed event or for every missed time-point

To assess incentive-related processing during prospective memory tasks, participants in the incentive group will be informed that they are initially endowed with 5 Swiss Francs (per prospective memory task) that they may lose proportionally to the number of prospective memory cues they miss (0.50 Swiss Francs per missed cue). They will also be informed that half of their earnings will be donated to an organization of their choice (Doctors without borders, UNICEF, or WWF).

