### Statistical analysis

#### Behavioural: Do loss-related incentives enhance prospective memory?

Since we are primarily interested in whether incentives will enhance prospective memory, we will report accuracy and mean response times for the event-based task as well as accuracy and clock checking for the time-based task as primary outcomes.

First, we will test whether incentives will improve task accuracy. We will use two-way mixed-design ANOVA on correctly remembered trials, with the within-subject factor ‘task type’ (event-based or time-based) and the between-subject factor ‘group’ (incentive or control). Next, we will test whether response times in the event-based task will become quicker with an incentive. We will use one-way ANOVA on response times for correctly remembered trials, with the between-subject factor ‘group’ (incentive or control). For time-based prospective memory, we will test whether an incentive influences how often participants check the clock. Similar to our previous study [36], we will divide the 30 s before and after each target time into four intervals: T – 30 refers to the interval 30 to 15 s and T – 15 to the interval 15 to 0 s before target time. T + 15 or T + 30 then correspond to the intervals 0 to 15 s and 15 to 30 s after the target time. We will use a two-way ANOVA with the within-subject factor ‘time-interval’ and the between-subject factor ‘group’ (incentive or control). Finally, we will test whether monthly income, retirement status, personality traits, reward sensitivity, executive functions, or daily life prospective memory will predict performance. We will use linear regression with prospective memory accuracy as dependent variable and scores from the questionnaires as predictors. Age and gender will be included as covariates in all statistical analyses.

We will use R (Version 4.2.1) with Rstudio (Version 2022.02.3) for statistical analyses, with *p* < 0.05 considered statistically significant. We will correct for multiple comparisons using Tukey’s method. Whenever the assumptions of normality or homogeneity are not met, data will be transformed and/or non-parametric alternatives will be used. In case of missing data, we will use linear-mixed effects models rather than ANOVAs.

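### A higher hit count in the incentive group cannot by itself be read as better prospective memory, because extra presses and 1-back costs are neither penalised nor analysed

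*Protocol article*

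**What the plan says.** Four statements in the protocol article bear on this point.

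- **Event-based scoring** (Prospective memory task): "Every answer that occurs within 5 s following the presentation of an animal will be considered as a prospective memory hit".
- **Time-based scoring** (same section): "Every correct response occurring ± 2.5 s around each target time will be counted as a prospective memory hit". Neither rule sets a condition on presses made outside the window.
- **Pay-off** (Fig. 2 legend): participants in the incentive group start each task with 5 Swiss Francs and "they will lose 0.50 Swiss Francs for every missed event or for every missed time-point". The paragraph after the legend describes the information given to participants in the same terms. No cost is stated for a false press or a 1-back error, and the control group has no pay-off.
- **Analysis** (Statistical analysis, Behavioural): accuracy in both tasks is among the primary outcomes, and "We will use two-way mixed-design ANOVA on correctly remembered trials", with group as the between-subject factor. The other primary outcomes are event-based response time and clock checking.

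False presses are not mentioned anywhere in the article. Correct 1-back answers are used to build fMRI regressors, but 1-back performance is not a behavioural outcome.

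**The concern.** The incentive gives one randomised group a reason to avoid misses and no stated reason to avoid superfluous presses or 1-back errors. Randomisation does not remove this, because it is part of what is randomised. A rise in hits then has at least three possible sources: better prospective memory, more pressing, or a shift of effort from the 1-back task to the cues. The planned behavioural outcomes cannot tell them apart.

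What is at stake is the conclusion that loss-related incentives enhance prospective memory, which the Discussion carries forward to real-life uses such as insurance bonuses. That Discussion lists alternative explanations for a null result but none for a positive one. The imaging is also touched: first-level regressors use the onset of every correct answer, so a lucky hit would enter the prospective memory contrast that is later compared between groups.

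**Working it through.** **Plan's own figures.** They are consistent. Cues: "10 prospective memory cues" × 0.50 = 5 Swiss Francs, the stated endowment. Block: mean picture time 2.5 s + mean interval 1.5 s = 4 s; 158 × 4 s = 632 s, or about 10.5 min. The sample size does not enter this point.

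**How much of the block is scored.** 10 windows × 5 s = 50 s; 50/630 = 7.9%. Presses in the remaining 92.1% have no stated effect on score or payment.

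**Limiting case.** A press every 5 s (630/5 = 126 presses) would score 10/10 in the time-based task and keep all 5 Francs. This shows what the rule permits, not what participants would do.

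**Illustration 1: random extra presses, time-based task.** Assumptions not in the documents: r random extra presses per minute, true accuracy 70%, between-person SD 1.5 to 3 cues. The chance that a missed cue becomes a hit is g = 1 − exp(−r × 5/60). Scored accuracy is 0.70 + 0.30g, the shift is 10 × 0.30 × g cues, and false presses per block are r × 10.5 × (1 − 50/630).

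| r | g | Scored accuracy | Shift (cues) | False presses | d (SD 3 to 1.5) | Significant at 0.05, 30 per group |
|---|---|---|---|---|---|---|
| 2 | 0.154 | 74.6% | 0.46 | 19 | 0.15 to 0.31 | 9% to 22% |
| 4 | 0.283 | 78.5% | 0.85 | 39 | 0.28 to 0.57 | 19% to 59% |
| 6 | 0.393 | 81.8% | 1.18 | 58 | 0.39 to 0.79 | 33% to 86% |

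The last column is a simple two-group comparison of time-based hits, not the planned mixed ANOVA.

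**Illustration 2: repeated presses around the minute.** Assume the intended press falls at X ~ N(0, SD) around the target. One press hits if |X| < 2.5 s. Presses at X − 5, X and X + 5 s hit if |X| < 7.5 s. If only the first of the three presses is scored, it hits when X lies between 2.5 and 7.5 s, so the probability is half the difference between the other two.

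| SD | One press | Three presses, any counts | Three presses, first counts |
|---|---|---|---|
| 3 s | 0.595 | 0.988 | 0.197 |
| 5 s | 0.383 | 0.866 | 0.242 |
| 8 s | 0.245 | 0.651 | 0.203 |

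Scoring the first press removes the gain from repeated pressing. These figures assume blind timing, which the clock makes unnecessary, so they show the mechanism only.

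**Event-based task.** No comparable figure is offered. Animals are visible cues, so extra pressing has less scope to turn misses into hits.

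**The case against.** The strongest reply has four parts.

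- **This is an article, not the full plan.** False-press handling could be in documents not shown, and the time-based rule does speak of a correct response. That is fair as to detail. But the hit rules, pay-off and accuracy variable are all stated, and nothing stated makes a hit depend on presses outside the window.
- **The clock is available on demand.** No cost is stated for checking it, and checking is surer than pressing repeatedly; clock checking is also compared by group. This stands, and it is why neither table estimates the bias.
- **Participants may not learn that extra presses are free.** The article does not say they are told the scoring window, and the Discussion rules out feedback during the task. This also stands, although someone unsure whether a press was in time can, under the stated rules, only gain by pressing again.
- **A shift of effort produces real detections.** Under randomisation, the group difference in hits is a valid effect on hits. Cues gained at the expense of the 1-back task were really noticed, and the Discussion itself anticipates that older adults may prioritise. This stands: that part concerns interpretation, not scoring.

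A reader might infer that the primary estimate is known to be biased towards the hypothesis, perhaps by as much as 38% to 87%. The documents do not support this. They give no press rates, timing errors or base accuracy, and that range assumes participants who do not use the clock.

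**Conclusion.** The point holds as a limit on interpretation. Under the stated scoring, pay-off and analysis, a higher hit count in the incentive group may include extra pressing, mainly in the time-based task, or prioritisation of cues over the 1-back task, and the planned outcomes cannot separate these from better prospective memory. The size is unknown. Under the assumptions shown, the artefact ranges from small (0.46 of 10 cues) to large enough to be declared significant in many trials (1.18 cues). This is a cheap improvement worth making before analysis; it does not show that the primary result is invalid.

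**What to change.** Keep hits as the accuracy outcome and prespecify:

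- **(a) One scored response per time-based target.** Take the first prospective memory press in the interval from 30 s before to 30 s after the target, which the clock-checking analysis already defines. Count it as a hit only if it lies within ±2.5 s. The ten intervals run from 0:30 to 10:30 without overlap and fit the block. Report the any-press score as a sensitivity analysis, since a stray early press would otherwise cancel a later correct one.
- **(b) Presses outside the hit windows, compared by group in both tasks.** Add a false-alarm-adjusted score such as d-prime as a sensitivity analysis for the event-based task. This assumes prospective memory presses can be told apart from 1-back answers; the text does not say whether the keys differ.
- **(c) 1-back accuracy and response time**, prospective memory blocks relative to ongoing-only blocks, compared by group.

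Conclude that prospective memory was enhanced only if the gain in hits is not accompanied by more false presses, and report any 1-back cost beside it as possible prioritisation.

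Two simpler scores should be avoided. Hits minus outside presses gives −10 to someone pressing 3 s late every minute and 0 to someone who forgets altogether. Taking the first press in each clock minute cuts through the window: a valid press at 1:01 would use up the second minute and discard a valid one at 1:59.

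The cost is a few extra models and slightly less direct comparability with earlier hit-only scores. No new data are needed, since hit scoring requires key presses and the fMRI regressors require 1-back correctness.

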**Fig. 2 Fig2:**
[figure not shown]
Procedure of the prospective memory paradigms. Each prospective memory task (i.e., event-based, or time-based) consists of an ongoing task (a 1-back task) either alone or in combination with a prospective memory task, where participants additionally need to respond to certain events (here: animals) or after a certain amount of time has passed (here: every minute). In the incentive group, participants will start with an initial amount of money (i.e., 5 Swiss Francs per task) and they will lose 0.50 Swiss Francs for every missed event or for every missed time-point

To assess incentive-related processing during prospective memory tasks, participants in the incentive group will be informed that they are initially endowed with 5 Swiss Francs (per prospective memory task) that they may lose proportionally to the number of prospective memory cues they miss (0.50 Swiss Francs per missed cue). They will also be informed that half of their earnings will be donated to an organization of their choice (Doctors without borders, UNICEF, or WWF).

### Monetary incentive delay task

To examine the neural substrates of incentive-related processing in the absence of prospective memory, participants will complete a modified version of the monetary incentive delay task [27, 35] that consists of a baseline and an incentive block.

At baseline, the participants will need to respond as fast and correctly as possible to triangles or squares and they will receive feedback (i.e., green tick = correct, red cross = incorrect or too late). Each trial will start with a fixation cross presented in the centre of the screen for 0.6—1.0 s. Then, either of the two stimuli will appear for 0.8 s, followed by another fixation cross (for 1.0—1.4 s) and feedback (for 0.5 s). After 20 trials, the mean response time of all correct answers will be calculated. Next, the incentive block will follow, during which the participants will again respond to triangles or squares (Fig. 3). In contrast to the baseline condition, however, they will be told that for some trials, it would now be possible to keep or lose an incentive. Each trial will start with the presentation of a fixation cross in the centre of the screen for 1—1.5 s, followed by a magnitude incentive cue for 2 s, and another fixation cross for 2—2.5 s. Then, participants will have to respond again to triangles or squares and, after another fixation cross, they will again receive feedback. The magnitude incentive cue will either be an empty white circle indicating a control trial, or a white circle with one horizontal line indicating an incentive trial. The two magnitude incentive cues will be presented 40 times each in randomized order. Hence, participants will complete a total of 80 trials. In order not to lose money, participants will need to answer correctly and faster than their mean response time during baseline. Control trials will be similar to the baseline condition. For incentive trials, answers that were correct and faster as during baseline will be indicated by a centime coin. A lost point (i.e., reaction time was slower than during baseline or an incorrect answer was given) will be indicated by a centime coin with a red cross. Below any 50-cent coin, the cumulative points will be shown. Participants will initially be endowed with an amount of 20 Swiss francs (40 points, each point corresponds to 0.50 Swiss Francs) and will be informed that they may lose it, depending on their response. We will encourage participants to respond as quickly as possible regardless of the type of the incentive cue. Comparable to previous studies, participants will have to keep more than 60% of total points (i.e., 24 points) to finally earn the incentive [27]. Otherwise, they will lose all the money. Again, half of their earnings will be donated to an organization of their choice.

**Fig. 3 Fig3:**
[figure not shown]
Procedure of the Monetary Incentive Delay task (baseline block not shown). The incentive block will consist of incentive trials and control trials. In each trial, participants will need to respond as fast and as correctly as possible to triangles or squares. During incentive trials (indicated by a circle with a horizontal line), they will be able to keep or lose points that will later be transferred to financial earnings. If they respond correctly and faster than during the baseline block, they will not lose a point (indicated by a centime coin). If they respond incorrectly or not fast enough, they will lose a point (indicated by a centime coin with a red cross). During control trials, it will not be possible to receive points, but participants will still receive feedback whether they responded correctly

### Statistical analysis

#### Behavioural: Do loss-related incentives enhance prospective memory?

Since we are primarily interested in whether incentives will enhance prospective memory, we will report accuracy and mean response times for the event-based task as well as accuracy and clock checking for the time-based task as primary outcomes.

First, we will test whether incentives will improve task accuracy. We will use two-way mixed-design ANOVA on correctly remembered trials, with the within-subject factor ‘task type’ (event-based or time-based) and the between-subject factor ‘group’ (incentive or control). Next, we will test whether response times in the event-based task will become quicker with an incentive. We will use one-way ANOVA on response times for correctly remembered trials, with the between-subject factor ‘group’ (incentive or control). For time-based prospective memory, we will test whether an incentive influences how often participants check the clock. Similar to our previous study [36], we will divide the 30 s before and after each target time into four intervals: T – 30 refers to the interval 30 to 15 s and T – 15 to the interval 15 to 0 s before target time. T + 15 or T + 30 then correspond to the intervals 0 to 15 s and 15 to 30 s after the target time. We will use a two-way ANOVA with the within-subject factor ‘time-interval’ and the between-subject factor ‘group’ (incentive or control). Finally, we will test whether monthly income, retirement status, personality traits, reward sensitivity, executive functions, or daily life prospective memory will predict performance. We will use linear regression with prospective memory accuracy as dependent variable and scores from the questionnaires as predictors. Age and gender will be included as covariates in all statistical analyses.

We will use R (Version 4.2.1) with Rstudio (Version 2022.02.3) for statistical analyses, with *p* < 0.05 considered statistically significant. We will correct for multiple comparisons using Tukey’s method. Whenever the assumptions of normality or homogeneity are not met, data will be transformed and/or non-parametric alternatives will be used. In case of missing data, we will use linear-mixed effects models rather than ANOVAs.

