### Sample size calculation

For the determination of sample size, we used G*power [40]. We based calculations on a previous study that used incentives to enhance event-based prospective memory [12]. The effect size in this study (Cohen’s *f* = 0.25) suggests that an inclusion of *n* = 54 participants would be needed to find such effects in a repeated measures design with two groups and five measurements with *α* = 0.01 and a power of 1-β = 0.99. To account for attrition, drop-out or exclusion due to movement artefacts, we plan to recruit *N* = 60 participants (*n* = 30 in each group).

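### The primary test of event-based response time adjusts for age and gender only and leaves out each participant's own block-1 1-back speed, which is already recorded; the cost is precision, not validity

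*Protocol article*

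**What the plan says.** All behavioural analyses are set out in the protocol article under *Behavioural: Do loss-related incentives enhance prospective memory?*

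- Primary outcomes: "we will report accuracy and mean response times for the event-based task as well as accuracy and clock checking for the time-based task as primary".
- Question for response time: "we will test whether response times in the event-based task will become quicker with an incentive".
- Model: "We will use one-way ANOVA on response times for correctly remembered trials, with the between-subject factor ‘group’ (incentive or control").
- Covariates: "Age and gender will be included as covariates in all statistical analyses". The response-time model is therefore group plus age plus gender.
- Significance level: "with *p* < 0.05 considered statistically significant".

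No measure of the participant's own speed is in this model. The executive-function scores appear only as predictors in a separate regression on accuracy.

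The design is under *Prospective memory task*: "During the first and the third block, participants will perform a 1-back working memory task (as an ongoing-task"). The prospective memory tasks occupy blocks 2 and 4, and "The order will be counterbalanced across participants". Block 1 thus precedes the event-based task for everyone. The first-level fMRI models, described under the heading on event-based versus time-based brain regions, use the onsets of correct answers in the ongoing-only block, so the timing of those responses is captured.

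Under *Sample size calculation*: "The effect size in this study (Cohen’s *f* = 0.25) suggests that an inclusion of *n* = 54 participants would be needed". The recruitment target is 60, 30 per group.

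**The concern.** The question is whether an incentive makes people faster, and it is answered by comparing response times between different people. In adults aged 60 to 75, stable differences in general speed can plausibly make up a good part of the between-person variance. Age and gender will remove some of that; the rest stays in the error term. A 1-back response time from the same scanner session is the obvious covariate to reduce it, and it needs no new measurement.

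The article uses each person's own baseline elsewhere: the monetary incentive delay task judges responses against the participant's mean baseline response time, and the imaging contrasts set prospective memory blocks against ongoing-only trials within person.

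At stake is the standard error of the group effect on a named primary outcome with at most 30 people per arm. A real speeding effect is more likely to be missed than it need be, and the estimate is not adjusted for any chance difference in speed between the arms beyond what age and gender explain.

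**Working it through.** **1. The article's own sample size.** Inputs from *Sample size calculation*: f = 0.25, two groups, m = 5 measurements, alpha 0.01, power 0.99. The correlation among repeated measures is not given; 0.5 with sphericity is assumed. For a within-subject or interaction effect:

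lambda = f² × N × m / (1 − rho) = 0.0625 × 54 × 5 / 0.5 = 33.75, on 4 and 208 degrees of freedom.

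Power is 0.992 at N = 54 and 0.989 at N = 52, so the stated 54 reproduces. The between-groups version of the same calculation needs 236. The stated calculation therefore does not describe the response-time test, which is a single between-group comparison, and the article gives no power for that test.

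**2. Power of the planned response-time test.** Assumptions: f = 0.25 carries over to response time, so d = 2f = 0.5; two-sided alpha 0.05. Let n be the number per group and k the number of covariates.

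- Noncentrality = d × √(n/2) / √(1 − r²), where r is the partial correlation of block-1 1-back response time with event-based response time after age and gender.
- Degrees of freedom = 2n − 2 − k, with k = 2 as planned and k = 3 with block-1 speed added.

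As planned (r = 0, k = 2):

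- n = 27: noncentrality 0.5 × √13.5 = 1.837, df 50, power 0.437.
- n = 30: noncentrality 0.5 × √15 = 1.936, df 56, power 0.477.

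**3. With block-1 speed added (k = 3).** The documents give no value of r, so a range is shown.

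| r | power, n = 27 | gain | power, n = 30 | gain |
|---|---|---|---|---|
| 0 | 0.437 | −0.0003 | 0.477 | −0.0002 |
| 0.3 | 0.471 | +0.034 | 0.514 | +0.036 |
| 0.4 | 0.502 | +0.065 | 0.546 | +0.069 |
| 0.5 | 0.548 | +0.110 | 0.594 | +0.116 |
| 0.6 | 0.615 | +0.177 | 0.662 | +0.185 |
| 0.7 | 0.713 | +0.276 | 0.759 | +0.282 |

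At r = 0.5 the residual variance falls by r² = 25%, which is worth 60 / 0.75 = 80 participants under the planned model instead of 60. A normal approximation gives similar figures at r = 0.5: 45.1% to 56.4% (n = 27) and 49.1% to 60.9% (n = 30).

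**4. Overlap with age and gender.** Because r is a partial correlation, a raw correlation of 0.5 may be worth less. Suppose age and gender alone explain part of the variance, and adding block-1 speed brings the total to only 25%:

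- Age and gender explain 5%: partial r² = 0.20/0.95 = 0.21, gain about 9 to 10 points.
- 10%: partial r² = 0.15/0.90 = 0.17, gain about 7 points.
- 20%: partial r² = 0.05/0.80 = 0.06, gain about 3 points.

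If the contributions are instead additive, the gain is about 12 to 16 points.

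**5. Which block can serve.** Block 3 always follows one prospective memory block, which the incentive group performs with money at risk, so block-3 speed is measured after the intervention. Block 1 precedes both prospective memory blocks. Whether it also precedes the incentive announcement is not stated.

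**The case against.** **The planned test is valid.** Allocation is random and stratified by education, age and sex. The group comparison is unbiased, and chance imbalance in speed is already covered by the type I error rate. This stands: a reader might infer that leaving out baseline speed biases the result, and the documents do not support that.

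**The model is not group-only.** The one-way ANOVA sentence, read alone, suggests no adjustment. The covariate sentence later in the same paragraph rules that out. This stands, and it is why the comparator above includes age and gender.

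**The gain is assumed, not known.** No correlation is given, and f = 0.25 comes from a study of incentives and event-based prospective memory with no mention of response time. Several design features could weaken the correlation: the outcome averages at most 10 cues, and only those remembered; a same/different judgement is not the same act as detecting an animal and carrying out an intention; and for some participants the event-based task comes in block 4, well after block 1. All this stands, so no single gain can be claimed as fact.

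**Block 1 may not be free of the incentive.** It is tempting to say that no money is at stake there. The article does not say so. The Fig. 2 caption places the ongoing-only part within each prospective memory task and makes the endowment per task, and the Discussion section on how incentives are processed has participants told at the start of the task. Losses depend only on missed cues, but knowing of them could change effort earlier; adjusting for block-1 speed could then remove part of the effect. This stands and makes the fix conditional.

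**Further covariates can be left to an analysis plan.** This carries less weight, because the article itself names the model and its covariates for this outcome.

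**Conclusion.** The point holds as one of efficiency. The model for a named primary outcome is fixed as group, age and gender, and it omits a recorded measure of individual speed that would probably sharpen the comparison. If d = 0.5 and two-sided alpha 0.05 are assumed, power is about 44 to 48% with 27 to 30 per group. The gain from block-1 speed runs from 3 to 4 points at a partial correlation of 0.3 to about 28 at 0.7, passing through 11 to 12 at 0.5; at zero almost nothing is lost. Even at 0.5 and 30 per group, power would be only 59%, so the covariate helps but does not make this a well-powered test.

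The size rests on two quantities the documents do not supply: the partial correlation, and whether f = 0.25 applies to response time. Use of the covariate in the primary model rests on a third, the timing of the incentive instruction. The change is worth making; the planned analysis is not wrong without it.

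**What to change.** In the behavioural analysis section, replace the one-way ANOVA on event-based response time with a pre-specified ANCOVA: group as the factor, with age, gender and the participant's mean correct 1-back response time from block 1 as covariates. Do not use block 3.

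State when the incentive group learns of the endowment. If that is after block 1, the ANCOVA is the primary analysis. If it is before block 1, keep the planned model as primary and report the adjusted model as a sensitivity analysis.

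The cost is a sentence or two of wording, one degree of freedom and a check of the instruction timing. No new data or participants are needed. The article describes data acquisition as ongoing, so at that stage the choice could still be fixed before any group comparison.

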### Study procedure

The study will consist of an online assessment of possible confounding factors using reliable and valid questionnaires as well as an on-site visit (Fig. 1). All participants will provide information on their monthly income, retirement status, monetary satisfaction and how often they donate money to charity. In addition, we will use the Edinburgh Handedness Inventory (EHI; [22]) to assess handedness and the NEO- Five Factor Inventory (NEO-FFI; [23]) to assess personality traits. To assess general sensitivity to reward or punishment, we will use the Behavioural Inhibition System/Behavioural Activation System Scales (BIS/BAS; [24]). Finally, to assess everyday prospective memory abilities, we will use the prospective and retrospective memory questionnaire (PMRQ; [25]) and the metacognitive prospective memory inventory (MPMI; [26]).

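### The regression of prospective memory accuracy on questionnaire scores leaves out randomised group, and the only multiplicity rule does not cover its slopes (minor)

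*Protocol article*

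**What the plan says.** The behavioural part of the Statistical analysis section of the protocol article describes three ANOVAs: accuracy, event-based response time and clock checking. Each names group (incentive or control) as a between-subject factor.

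A regression follows. Its aim is stated as "Finally, we will test whether monthly income, retirement status, personality traits, reward sensitivity, executive functions, or daily life prospective memory will predict performance", and its model as "We will use linear regression with prospective memory accuracy as dependent variable and scores from the questionnaires as predictors". The covariate rule is "Age and gender will be included as covariates in all statistical analyses". The threshold is "with *p* < 0.05 considered statistically significant", and the one multiplicity rule begins "We will correct for multiple comparisons using Tukey".

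The regression text does not name group and is not limited to one arm. By contrast, the imaging section on event-based versus time-based memory explicitly confines its paired t-tests to the control group. The article also does not say how many scores enter, whether they enter together or one at a time, or which task's accuracy is the outcome.

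**The concern.** There are two separate issues.

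**Group.** The Background predicts that having to avoid losing an incentive improves prospective memory, and accuracy is this regression's outcome. A model without group leaves that effect in the error term. Only the incentive arm has money at stake in the memory tasks, so a single reward-sensitivity slope is an average over two different situations.

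**Multiplicity.** Tukey's method compares pairs of means. It gives no adjustment for a set of regression coefficients. Several trait slopes would therefore each be tested at 0.05, in an analysis not labelled exploratory, and a chance finding could be reported as a determinant of prospective memory in older adults.

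**Working it through.** **Plan's own figures.** The article gives no error rate or sample-size basis for the regression. The available N comes from the Sample size calculation section: 54 needed, 60 recruited (30 per arm), from f = 0.25, two groups, five measurements, alpha 0.01 and power 0.99. Assuming a within-person correlation of 0.5 and sphericity (neither is stated), 54 reproduces for the within factor or the group-by-measurement interaction, with power 0.992. It does not reproduce for the between-group factor, which would need 236. Using f = 0.25 as the size of the group effect below is therefore an assumption.

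**Cost of omitting group**
- Share of variance at f = 0.25: f²/(1 + f²) = 0.0625/1.0625 = 0.059.
- Inflation of standard errors: 1/√(1 − 0.059) = 1/√0.941 ≈ 1.03, about 3%.
- Bias: allocation is random, so group is unrelated in expectation to traits that the incentive does not itself change. Their slopes are not biased by leaving it out.
- Averaging: if the reward-sensitivity slope were b in the incentive arm and 0 in the control arm, the pooled slope at 1:1 allocation would be about b/2.

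**Number of slopes tested**
- One score per named domain: income, retirement status, personality, reward sensitivity, executive functions, everyday prospective memory = 6. With age and gender, 8 terms.
- One score per scale (assumed): income 1 + retirement 1 + personality 5 (from "Five Factor Inventory (NEO-FFI; [23]) to assess personality traits") + inhibition and activation scales 2 + Trail Making 1 + Digit-Symbol 1 + two everyday-memory inventories 2 = 13. With age and gender, 15 terms, or 54/15 = 3.6 to 60/15 = 4.0 people per term.

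**Chance of at least one false predictor.** This takes two-sided 0.05 tests (sidedness is not stated) and assumes no score is truly related to accuracy. If tests were independent the chance is 1 − 0.95^k. The joint-model column comes from simulated least-squares fits with two covariates, N = 54 and 60, predictor correlations 0, 0.3 and 0.5, and 4,000 runs per setting.

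| Scores tested | Independence formula | One joint model |
|---|---|---|
| 6 | 0.265 | 0.24 to 0.25 |
| 10 | 0.401 | 0.36 to 0.37 |
| 13 | 0.487 | 0.43 to 0.44 |

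With 13 separate regressions at N = 60 (800 runs each) the chance is 0.42 to 0.50. In the joint models each single slope keeps its 5% error rate (0.047 to 0.052).

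**Does omitting group drive that chance?** With 13 scores and N = 60, a true group effect of d = 0.5 gives 0.443 without group and 0.442 with it. At d = 0.8 the figures are 0.445 and 0.443. It does not.

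**Effect of adjustment.** A Bonferroni threshold of 0.05/13 = 0.0038 brings the chance to at most 0.05. Holm's procedure gives the same guarantee.

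**The case against.** The strongest reply is that this is a supporting analysis described in two sentences of a condensed article. The full model may name group, and nothing in the text excludes it. Omission costs about 3% in standard errors on an assumed effect size, and every test of the incentive effect already contains group. That fixes the point as minor. It does not remove it, because the article does specify the regression's outcome, predictors, covariates, threshold and multiplicity rule, and group is absent only there.

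A reader might infer more than the document supports:
- *That pooling the arms, or having few people per term, produces the false predictors.* It does not. The chance depends on how many slopes are tested without adjustment. Few people per term costs precision and stability.
- *That the model has at least 15 terms.* The article gives no count. It names reward sensitivity only, so an inhibition score need not enter, and it calls the predictors questionnaire scores although the executive measures are tests.
- *That the model is over-fitted, with an expected R² of 15/59 = 0.25 to 15/53 = 0.28 under no association.* This holds only for one joint 15-term model. The article does not say that the scores enter together or that R² will be interpreted.
- *That a reward sensitivity by group interaction is required.* The stated question is whether traits predict performance, not whether they predict response to the incentive.

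**Conclusion.** The point holds as a minor one, in two independent parts.

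1. The regression as written omits randomised group. This costs some precision and makes a reward-sensitivity slope hard to interpret, without biasing trait slopes in expectation. The 3% figure rests on treating f = 0.25 as the between-group effect.
2. The slopes have no multiplicity control, because the stated method does not apply to them. The chance of at least one false predictor is about 0.25 with 6 scores and 0.43 to 0.44 with 13, provided no score is truly related to accuracy. Both counts are assumptions about scoring.

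No conclusion about whether incentives improve prospective memory depends on this regression.

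**What to change.** - Add group to the regression.
- Name in advance the scores that will be tested. Then either apply Holm's adjustment across them or label the regression exploratory.
- State which accuracy is the outcome. If both tasks are analysed together with a task-type term, use a mixed model, because each person contributes two accuracy values and ordinary regression would treat them as independent.
- A reward sensitivity by group term may be added as an optional, exploratory analysis.

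The group term costs one degree of freedom. Holm's adjustment costs some power for individual traits; the exploratory label avoids that but limits what may be claimed. The Study status section reports that data acquisition is ongoing, so the wording can be settled before the analysis is run.
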